### Statistical analysis

Baseline and post intervention measures will be reported as means (m) ± standard deviations (SD). Data will be analysed on an intention to treat basis. Change in the selected primary outcome measure and secondary outcomes will be evaluated using two way Repeated Measures ANOVA to determine group main effect, time main effect, and interaction effect between group and time. Level of significance will be set at P < 0.05. Participants in the exercise intervention group will be grouped according to high adherence (> median adherence for the full group) and low adherence (≤ median adherence level). Repeated measures ANOVA will be used to determine whether there is a difference in change in the primary and secondary balance measures between the high adherence and low adherence group.

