**Methods/Design:**

A single blind randomized controlled trial will be conducted, with assessors blind to group allocation. Study participants will be aged 50 years and above, living in the community and have been identified as having impaired turning ability [outside of age and gender normal limits on the Step Quick Turn (180 degree turn) task on the Neurocom® Balance Master with long plate]. After a comprehensive baseline assessment, those classified as having balance impairment while turning will be randomized to intervention or control group. The intervention group will receive a 16 week individualized balance and strength home exercise program, based on the Otago Exercise Program with additional exercises focused on improving turning ability. Intervention group will attend four visit to the assessment centre over 16 weeks period, for provision, monitoring, modification of the exercise and encourage ongoing participation. Participants in the control group will continue with their usual activities. All participants will be re-assessed on completion of the 16 week program. Primary outcome measures will be the Step Quick Turn Test and Timed-Up and Go test. Secondary outcomes will include other clinical measures of balance, psychological aspects of falls, incidence of falls and falls risk factors.

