**Assessments – force platform**		
Modified Clinical Test of Sensory Interaction Balances (mCTSIB)	√	√
Limits of Stability (LOS)	√	√
Sit to Stand (STS)	√	√
Walk across (WA)	√	
Step quick turn (SQT)	√	√

All of the measures being used in this study have been shown to have moderate to high reliability and validity in a variety of older and clinical populations [17-20]. Assessments will be conducted by a trained assessor blind to group allocation.

Measures of fall risk and fall risk factors;

i. A retrospective recall about any falls in the preceding 12 months. The information regarding history of fall such as date, location, activity at the time of fall, obstacles involved in the fall, any warning sign or symptoms, type of injuries and medical attention sought after fall will be retrieved for each of fall event (details for up of 4 falls will be retrieved).

ii. Falls Risk assessment for Older People in the Community (FROP-Com) [19], a detailed assessment of 13 falls risk factors. Each domain of the assessment describes an evidence based fall risk factor among community dwelling older adults, and each domain is scored to reflect graded risk (nil, mild, moderate, severe). The FROP-Com has been shown to have good retest reliability (ICC for intra-rater and inter-tester reliability were 0.93 and 0.81 respectively) [21] and moderate accuracy predicting falls (sensitivity 71% and specificity 56%) [21]. A total score between 0 and 60 will be obtained, where higher scores indicate greater level of risk of falling.

iii. Activity level will be monitored in both groups at baseline and 16 weeks using the Human Activity Profile (HAP) [22]. The Adjusted Activity Score (AAS) will be used, calculated by subtracting the number of items listed as “stopped doing” from the highest numbered item listed as “still doing”. This will enable identification of any unanticipated change in activity/exercise level in the control group during the 16 week trial; as well as monitor any change in activity level by the intervention group.

iv. Psychological aspects related to falls will be measured using Falls Efficacy Scale-International (FES-I) short version-7 items [23] to assess the level of fear of falling. Level of depression will be measured using the 15 item Geriatric Depression Scale [24].

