### Primary outcome measure

The primary outcome will be the Step Quick Turn test (Neurocom® Balance Master) (a laboratory measure) (amount of sway-degrees/s) and Timed Up and Go Test (a clinical measure). Other measures of balance and mobility performance, falls efficacy, and adherence to exercise program will be considered as secondary outcomes. While falls data is being collected, the study is not powered sufficiently to identify a significant difference in falls between the two groups.

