Finally, there has been little falls prevention intervention programs conducted in Malaysia, and there is some evidence to suggest that interventions effective in Western countries (where the majority of falls prevention research has been carried out) may not always be translatable to Asian countries [44]. Differences in socioeconomic, cultural, behavioral and environmental factors may all impact upon the likely success of interventions between different countries. This study will provide some valuable local data regarding risk factors for falls among older community dwelling Malaysians, and the acceptability of this type of home exercise program in the Malaysian context. This study is proposed to provide a basis for planning future fall prevention interventions of relevance to specific identified falls risk in the Malaysian population.

There are several elements of our proposed method that have been adopted to accommodate the limited timelines and resourcing available for the project. There is some debate in the research literature relating to the accuracy of self-report measures of physical activity, and that accelerometers provide a more objective and valid measure [45]. The Human Activity Profile self-report measure selected for use in this project has been extensively used in research, and has been shown to be reliable and valid [46]. The duration of follow up for this study was limited to immediately following the four months intervention, instead of the recommended 12 month follow up for fall prevention studies [47]. Falls data is being collected as a secondary outcome measure to inform future study power calculations, however the study is not powered to detect a significant difference on the falls measure. These limitations are not expected to impact on the overall project aim of evaluating the effectiveness of this exercise program in improving turning performance.

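### The status of falls is inconsistent and, if they are a secondary outcome, the ANOVA-on-change and LOCF rules as written would set a 12-month recall against a 16-week count

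*Protocol article*

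**What the plan says.** All references are to the protocol article.

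- **Status of falls.** Abstract, Methods/Design: "Secondary outcomes will include other clinical measures of balance, psychological aspects of falls, incidence of falls and falls risk factors". Discussion: "Falls data is being collected as a secondary outcome measure to inform future study power calculations". The section Primary outcome measure gives a different list: "Other measures of balance and mobility performance, falls efficacy, and adherence to exercise program will be considered as secondary outcomes". It then treats falls separately: "While falls data is being collected, the study is not powered sufficiently to identify a significant difference in falls between the two groups".
- **Analysis.** Statistical analysis: "Change in the selected primary outcome measure and secondary outcomes will be evaluated using two way Repeated Measures ANOVA". The rule tests group, time and their interaction. It makes no exception for counts.
- **Missing data.** Losses to follow-up are imputed by last value carried forward, again with no exception.
- **Falls before randomisation.** Measures and procedures: "A retrospective recall about any falls in the preceding 12 months", with a limit on descriptive detail ("details for up of 4 falls will be retrieved"). Table 1 gives the same 12-month window in its baseline column.
- **Falls after randomisation.** Table 1 has participants asked at each phone call about the preceding 3 weeks, with a falls diary at 16 weeks. Follow up data collection places the calls at weeks 4, 8, 12 and 16.

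**The concern.** An analysis of change needs a baseline value and a follow-up value on the same scale. For falls the only available pair is a retrospective count over 52 weeks and a prospectively collected count over 16 weeks. The two differ in exposure by a factor of 52/16 = 3.25 and also in how falls are ascertained. Falls are moreover sparse, skewed counts, which a normal-theory ANOVA fits poorly.

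Carrying the last value forward adds to this. For a participant lost before any falls report, the last value is the 12-month count.

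At stake is the use the Discussion gives for these data, the planning of later trials. That calls for a fall rate per person-time and its dispersion. The concern is not that a falls model is missing from a condensed article. It is that the general rules, as worded, reach an outcome they do not suit.

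**Working it through.** The protocol states no fall rate or expected number of falls, so there is no falls figure to reproduce.

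**Inputs from the protocol:** baseline window 12 months (52 weeks); follow-up 16 weeks; anticipated dropout 20%; 34 per group.

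**Assumptions, not in the protocol:** constant fall rate; full recall unless stated; for the simulation, 0.3, 0.5 and 1.0 falls per person-year, negative binomial with dispersion 1.

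**1. Time effect, no dropout.** Expected ratio of follow-up to baseline count = 16/52 = 0.308. Apparent drop = 1 - 0.308 = 69.2%. This does not depend on the fall rate.

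**2. Time effect with LOCF.** If a fraction d is lost before any falls report and the 12-month count is carried forward, apparent drop = 1 - [(1 - d) × 16/52 + d].

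| d | Apparent drop |
|---|---|
| 0% | 69.2% |
| 10% | 62.3% |
| 20% | 1 - (0.246 + 0.200) = 55.4% |
| 30% | 48.5% |

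**3. Sensitivity to recall, no dropout.** With 80% of baseline falls recalled: 1 - 0.308/0.8 = 61.5%. With 60%: 1 - 0.308/0.6 = 48.7%.

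**4. What the tests would do.** Two-time-point ANOVA, 34 per group, 20,000 simulated trials, no true change in rate and no intervention effect:

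| Dropout | Time effect rejected (0.3 / 0.5 / 1.0 falls per year) | Group-by-time rejected, range over rates |
|---|---|---|
| None | 77% / 93% / 99.8% | 4.6 to 5.2% |
| 20% in both arms, LOCF | 66% / 87% / 99% | 4.5 to 4.9% |
| 30% vs 10% (assumed), LOCF | 66% / 87% / 99% | 5.4 to 7.3% |

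In the last row the interaction is shifted against the arm with more dropout by (0.30 - 0.10) × rate × (1 - 16/52). That is 0.04 falls per person at 0.3 per year and 0.14 at 1.0.

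**5. Noise in the group-by-time test.** With two time points this test compares change scores. Let r be the annual rate, f = 16/52 and k the dispersion, with each person's underlying rate shared across both periods.

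- Variance of change = r(1 + f) + k r²(1 - f)²
- Variance of the 16-week count = r f + k r² f²
- Ratio at k = 0: 1.308/0.308 = 4.25
- Ratio at r = 1.0, k = 2: (1.308 + 0.959)/(0.308 + 0.189) = 4.56

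The standard error is therefore about 2.1 times that of a direct comparison of 16-week counts (square roots 2.06 and 2.14).

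**6. Coverage of the follow-up window.** Four calls, each asking about 3 weeks, cover 4 × 3 = 12 of 16 weeks. The diary may close the gap, but the text does not say which source defines the count.

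**The case against.** The strongest reply is that the protocol never says it will do this. No sentence makes the 12-month recall the baseline of a falls change score. Table 1 lists falls history in its screening block, and the follow-up entry describes surveillance rather than a repeat of the same measure. The section Primary outcome measure keeps falls out of its secondary list. The ANOVA rule also cannot be literal for every secondary outcome: adherence is on that list, yet it is recorded only in the intervention group and has no baseline. A natural reading is that ANOVA covers measures taken at both visits. All of this stands. The unequal comparison is what the rule yields if applied to falls as worded, not a declared intention.

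A reader might infer that the trial would report a false 69% reduction in falls, or a false benefit of exercise. The documents do not support either. The 69% is the no-dropout figure, and it belongs to the time effect in both arms alike. The group-by-time test keeps its nominal error rate unless dropout differs by arm.

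Nor does LOCF inflate every dropout's count 3.25-fold. That applies only to people lost before any falls report. Later losses already have a post-randomisation value, and carrying that forward could understate their falls.

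It is also fair that a mean count over a full 16 weeks converts to a rate for completers, so the planned summaries would not be useless. What does not stand is leaving the whole matter to an analysis plan. The status of falls is contradictory in this document, and the two general rules are stated here without exception.

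**Conclusion.** The point holds in a limited form and is worth correcting. The Abstract and Discussion conflict with the section Primary outcome measure on whether falls are secondary. If they are, the stated rules give a time effect dominated by window length: an apparent drop of 69% with no dropout, and about 55% if all of the anticipated 20% are lost before any falls report. Both figures assume a constant rate and full recall; under-recall at baseline makes them smaller.

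The group-by-time test loses precision, with a standard error roughly doubled under the rates and dispersion assumed. It is biased only if LOCF meets unequal dropout, and then modestly in the case examined. The primary conclusions on turning and Timed Up and Go are untouched, and falls are openly declared unpowered. The consequence is confined to the quality of the falls estimates.

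**What to change.** 1. State once whether falls are a secondary or an exploratory outcome, and align the Abstract, Primary outcome measure and Discussion.
2. Exempt falls from the repeated measures ANOVA and from LOCF.
3. Compare falls during the 16 weeks between groups as an exploratory count analysis with log observed person-time as offset, using Poisson regression with robust standard errors or negative binomial regression. Enter prior-year falls as a covariate only if the number of events allows. Report the rate per person-year by group and the rate ratio with 95% CI.
4. Reconcile the 3-week recall window in Table 1 with calls at weeks 4, 8, 12 and 16, and say how calls and diary combine, so that person-time is defined.

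The cost is a few sentences and no new data. The downside is imprecision: at the assumed 0.3 to 1.0 falls per person-year, 34 people over 16 weeks yield 34 × 16/52 × rate, or about 3 to 10 falls per group. A negative binomial model with a covariate may be fragile at those numbers, so the simpler model should be allowed for in advance.

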### Participants

Participants will be recruited from the membership of the University of Third Age (U3A) of Malaysia, on a voluntary basis. The age of 50 years and above will be used in this study as a criterion for defining “older people” (instead of the more commonly used age of 60 years and above), due to the lower life expectancy in Malaysia (72 years for males and 78 years for females [16]) compared to Western countries. Recruitment of participants will be through distribution of flyers to all U3A members.

Potential participants will be screened on a single occasion prior the baseline assessment to ensure they meet the study inclusion criteria. Participants will be included in the trial if they meet all of the inclusion criteria: i) identified having unsteadiness during turning Neurocom® Balance Master with long plate, and if performance is outside of normal limits (based on normative data based age and gender limits in the Neurocom® system); ii) community-dwelling; iii) aged 50 years and over; iv) able to tolerate standing and walking independently for at least six minutes and community ambulant (able to walk independently outdoors without support or not needing more than a single point stick; v) no other major neurological history (e.g. stroke with unilateral or bilateral paresis, multiple sclerosis) or orthopaedic history that impacts on functional mobility.

Participants will be excluded if they: i) have severe clinical or musculoskeletal impairments (eg; previous fractures) affecting mobility; ii) have visual or auditory impairments which cannot be corrected; iii) have a past history of stroke, Parkinson’s disease, cardiac problems, or transient ischemic attacks; iv) are aged less than 50 years old; v) use a walking frame, crutches or other bilateral support gait aids for walking in the community; vi) are not community ambulant (not able to walk outdoors away from home independently); and vii) are institutionalized (living in residential care).

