### Sample size

Power analysis was performed for the primary outcome measure (Step Quick Turn test on the Neurocom® Balance Master), using the mean score for the Step Quick Turn test (sway-degrees/s) results from a previous exercise intervention trial of older people with mild balance impairments [34]. It was estimated that 34 participants per group (68 participants in total) would be required to have at least 80% power to detect a 15% improvement in the Step Quick Turn test using the turn sway measure on the Neurocom Balance Master long-plate (degrees/s), (assuming 50% standard deviation improvement with the intervention [sd = 10.2, effect size = 0.5] at P < 0.05 (two-tailed). This calculation includes allowance for an anticipated 20% dropout rate. This sample size should also be adequate for other secondary outcome measures including the Limits of Stability test (Neurocom® Balance Master), the Step Test, and Functional Reach Test.

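### The planned repeated measures ANOVA lists three effects without naming the one that tests the intervention, and its one valid treatment term is no more efficient than baseline-adjusted ANCOVA

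*Protocol article*

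**What the plan says.** The Statistical analysis section opens with "Change in the selected primary outcome measure and secondary outcomes will be evaluated" and gives the method as "two way Repeated Measures ANOVA to determine group main effect, time main effect, and interaction effect between group and time". It adds "Level of significance will be set at P < 0.05". The three effects stand on an equal footing, and baseline enters only as the first of the two repeated measures.

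Other sections that bear on this:
- **Timing.** Table 1 (Measures and procedures) has Step Quick Turn and Timed Up and Go at baseline and 16 weeks only. The Randomization section places allocation after the baseline assessment.
- **Entry.** The Participants section admits people on the Neurocom turning test "if performance is outside of normal limits (based on normative data based age and gender limits in the Neurocom® system". The Abstract (Methods/Design) says "those classified as having balance impairment while turning will be randomized to intervention or control group".
- **Primary outcomes.** The Primary outcome measure section names Step Quick Turn sway and Timed Up and Go.
- **Size.** The Sample size section gives "34 participants per group (68 participants in total" for "at least 80% power to detect a 15% improvement in the Step Quick Turn test", with "sd = 10.2, effect size = 0.5] at P < 0.05 (two-tailed". It states no pre-post correlation and does not tie the calculation to any ANOVA term.

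**The concern.** Two of the three listed effects do not estimate the treatment effect.

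The group main effect averages a score taken before randomization with the 16-week score, so it dilutes the answer. The time main effect is not a comparison between arms at all. People enter because of an out-of-limits result on the test that also supplies a primary outcome, so some improvement in both arms is plausible even if exercise does nothing; practice acts in the same direction. If a significant main effect were reported as benefit, the conclusion would not rest on the randomized comparison.

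The interaction does rest on that comparison. With two time points, however, it is the unadjusted comparison of change scores, which can discard information that the baseline measurement already provides.

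**Working it through.** **Inputs.** From Sample size: d = 0.5, SD 10.2 deg/s (target 0.5 × 10.2 = 5.1 deg/s), two-sided 0.05, 34 per group, 20% dropout (34 × 0.8 ≈ 27 completers). Assumed, because the documents do not give it: r from 0.5 to 0.8. Powers are from the noncentral t and assume complete data.

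**The plan's own figure.** A two-sample comparison needs n = 2(1.96 + 0.842)²/0.5² ≈ 63 per group (64 by t), or 63/0.8 ≈ 79 (80 by t) with dropout. The stated 34 is not reproduced this way. A change-score test gives 27/0.8 ≈ 34, but only with an unstated r of about 0.8. That is a separate point on sample size; here 34 is taken as given.

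**What each effect estimates.** Let the treatment effect be δ. Baseline means are equal in expectation because allocation follows baseline.
- Group main effect: (0 + δ)/2 = δ/2.
- Time main effect: the common shift over time plus δ/2, pooled over arms.
- Interaction: δ, the between-arm difference in change.

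**Standardized effects, equal baseline and follow-up SDs.**
- Group: 0.25/√((1 + r)/2)
- Interaction: 0.5/√(2(1 − r))
- ANCOVA: 0.5/√(1 − r²)

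At r = 0.5 these are 0.289, 0.500 and 0.577. The ANCOVA-to-change variance ratio is (1 − r²)/(2(1 − r)) = (1 + r)/2.

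| r | Variance ratio | Group, 34/arm | Interaction, 34/arm | ANCOVA, 34/arm | Interaction, 27/arm | ANCOVA, 27/arm |
|---|---|---|---|---|---|---|
| 0.5 | 0.75 | 22% | 53% | 65% | 44% | 55% |
| 0.7 | 0.85 | 20% | 75% | 81% | 64% | 71% |
| 0.8 | 0.90 | 19% | 89% | 92% | 81% | 85% |

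**Without equal SDs.** With baseline SD σ₀ and follow-up SD σ₁, change variance minus ANCOVA residual variance is (σ₀² + σ₁² − 2rσ₀σ₁) − σ₁²(1 − r²) = (σ₀ − rσ₁)², which is never negative. ANCOVA is therefore never less efficient, apart from one residual degree of freedom.

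**Allowing for selection.** Suppose, as an extreme illustration, that baseline sway is normal and truncated to the worst 5%. Its variance falls to 0.138 of the unselected value. In unselected-SD units, change variance is (1 − r)² × 0.138 + (1 − r²), and ANCOVA variance is 1 − r².
- r = 0.5: 0.0345 + 0.75 = 0.7845; saving 0.0345/0.7845 = 4.4%; power at 34 per arm 63% vs 65%.
- r = 0.7: 0.0124 + 0.51 = 0.5224; saving 0.0124/0.5224 = 2.4%; power 80% vs 81%.

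Truncation at 1 SD gives savings of about 2–6% over r = 0.8 to 0.5.

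**If main effects were read as benefit.** In 20,000 simulated trials per setting with no treatment effect and 34 per arm, the interaction alone is significant in about 5%. With no common shift, interaction or group is significant in about 9.5%, and any of the three in about 14%. An assumed common shift of 0.3 SD makes the time effect significant in 68% (r = 0.5) to 88% (r = 0.7).

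**The case against.** The strongest reply is that the valid test is already in the plan. The interaction is listed, the section speaks of change, and its adherence analysis asks about a difference in change, which is an interaction reading. Nowhere does the article say that a time or group main effect would count as benefit. A two-group, two-time repeated measures ANOVA gives an unbiased 5% test through its interaction, and preferring ANCOVA is a matter of efficiency. An unseen analysis plan might name the decisive contrast. All of this stands, except that the article does fix the model and its list of effects: a later plan would have to change that choice, not just fill a gap.

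A second reply is that strong selection on baseline and a large ANCOVA gain do not go together. This also stands: the 25% and 15% variance savings at r = 0.5 and 0.7 need equal variances, and strict truncation leaves only a few per cent.

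A reader might infer that regression to the mean would by itself produce an improvement as large as the 5.1 deg/s target. The documents do not support any such size:
- They do not say whether turn time or sway must be out of limits.
- The Participants section puts screening before the baseline assessment, while the Abstract classifies people after it, so it is unclear whether the qualifying value is also the analysed baseline.
- The cut-off and the test-retest reliability are not given.
- The SD of 10.2 is tied to an earlier trial in mildly impaired people, so it cannot be taken as an unselected-population SD.

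**Conclusion.** The point holds as one of clarity and efficiency. Three effects are listed without rank, and only the interaction is an unbiased treatment comparison. The group effect is halved in expectation, with power of about 19–22% at d = 0.5 and 34 per group. The time effect is not a treatment comparison, and the size of any shared shift cannot be determined from the documents.

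Replacing the interaction by ANCOVA gains about 12 percentage points of power at r = 0.5, 7 at r = 0.7 and 3 at r = 0.8 under equal variances. Under strict truncation of baseline sway to the worst 5% it gains 1 to 2 points (r = 0.7 and 0.5). The gain thus depends on an unstated correlation and on how sharply entry truncates sway.

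Two stronger conclusions are tempting and do not follow. The planned analysis is not invalid: its interaction keeps the 5% level, and error inflation arises only if a main effect is read as benefit. Nor does ANCOVA rescue the sample size: with 27 completers per group, 80% power still needs r of about 0.77, against about 0.80 for the change score.

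**What to change.** In the Statistical analysis section, define the primary analysis as an ANCOVA of 16-week Step Quick Turn sway on group, adjusted for baseline sway, and report the adjusted between-group difference with its 95% CI. Use the same model for Timed Up and Go and for the continuous secondary outcomes, each adjusted for its own baseline. State that group main effects, time main effects and within-group changes will not be interpreted as evidence of effectiveness.

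The cost is a change of wording and one residual degree of freedom per model. Table 1 already collects the outcomes at baseline, so no extra participants or visits are needed. The sample size, the last-value-carried-forward rule and the use of two primary outcomes need separate attention.

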### Follow up data collection

Intervention group participants will be asked to complete a daily log of their exercise participation, to be used to calculate exercise adherence. Both the intervention and control group will receive four phone calls interspersed over the 16 week period (weeks 4, 8, 12 and 16) by a researcher to obtain details regarding any falls that occurred between phone contacts.

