### Missing data

Missing data (due to loss to follow up) will be imputed using the last value carried forwards method [35].

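### Carrying baseline values forward into the adherence analysis can bias the high- versus low-adherence contrast toward a benefit of adherence

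*Protocol article*

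**What the plan says.** The Statistical analysis section divides exercise participants into "high adherence (> median adherence for the full group) and low adherence (≤ median adherence level"). Repeated measures ANOVA is then used to test "whether there is a difference in change in the primary and secondary balance measures between the high adherence and low adherence group". The same section sets P < 0.05 and states, without exempting this analysis, "Data will be analysed on an intention to treat basis".

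The Missing data section is equally general: "Missing data (due to loss to follow up) will be imputed using the last value carried forwards method".

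On timing, the abstract says "All participants will be re-assessed on completion of the 16 week program", and Table 1 shows the follow-up balance and mobility tests at baseline and 16 weeks, with nothing between. Adherence comes from the diary: exercise participants "complete a daily log of their exercise participation, to be used to calculate exercise adherence" (Follow up data collection). On losses, the Sample size section says "This calculation includes allowance for an anticipated 20% dropout rate".

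**The concern.** Each rule is familiar on its own. The difficulty comes from combining them. With no assessment between baseline and 16 weeks, the last value of anyone lost to follow-up is the baseline value, so the imputed change is zero. Someone who leaves early has usually logged fewer sessions, and so tends to sit at or below the median. The zero changes then collect in the low-adherence half and pull its mean change toward nothing, whatever adherence truly does.

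At stake is how one secondary analysis is read. A high-versus-low difference could be taken as evidence that doing more of the programme improves turning, when part of it comes from the imputation. The comparison of exercise with control does not depend on this contrast.

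**Working it through.** The plan gives no figure for the adherence contrast, so the check uses its planning values. Whether 34 per group is itself right is a separate question; it is taken as given here.

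**Inputs from the Sample size section**
- Exercise arm: 34, so 17 low and 17 high if there are no ties.
- Dropout: 20%, and 0.20 × 34 = 6.8, about 7.
- SD 10.2 deg/s and effect size 0.5, so the target improvement is 0.5 × 10.2 = 5.1 deg/s.
- Two-sided 5% level.

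**Assumptions, not in the documents**
- Every completer improves by the same amount on average, whatever the adherence, so the true high-minus-low difference is 0.
- Baseline to 16-week correlation ρ of 0.5, 0.7 or 0.8. The SD of change is 10.2 × √(2(1 − ρ)), which gives 10.2, 7.9 and 6.5 deg/s.
- The division of the 7 dropouts between the halves, which is varied.

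**Expected gap.** With mean improvement μ in completers, and d_L and d_H dropouts in the low and high halves:

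gap = μ × (17 − d_H)/17 − μ × (17 − d_L)/17 = μ × (d_L − d_H)/17

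With μ = 5.1 and all 7 in the low half, the low-half mean is 5.1 × 10/17 = 3.0 against 5.1 in the high half. The gap is 2.1 deg/s, or 2.1/5.1 = 41% of the target effect.

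**False-positive rate.** With two time points, the group-by-time test in the repeated measures ANOVA equals a t-test on change. Simulation (40,000 runs per scenario) with dropouts' change set to 0 and μ = 5.1 gives:

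| Dropouts low / high | Gap (deg/s) | Rejection, ρ = 0.5–0.7 |
|---|---|---|
| 7 / 0 | 2.1 | 10–13% (17% at ρ = 0.8) |
| 6 / 1 | 1.5 | 7–8% |
| 5 / 2 | 0.9 | 5–6% |
| 4 / 3 | 0.3 | 4–5% |

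If the dropouts are spread at random over the two halves, the expected gap is 0 and rejection is about 5%.

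**Sensitivity, all dropouts in the low half, ρ = 0.5–0.8**
- μ = 2.55 (half the target), 20% dropout: gap 2.55 × 7/17 ≈ 1.0, rejection 6–8%.
- μ = 0: gap 0, rejection about 5%.
- μ = 5.1, 10% dropout (3 people): gap 0.9, rejection 6–7%.
- μ = 5.1, 30% dropout (10 people): gap 3.0, rejection 17–32%.

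**Without carried-forward values.** Splitting only participants with an observed 16-week value gives an expected gap of 0 and rejection of 4.9–5.2%. This isolates the cause: the halves are still formed by a median split, and the bias has gone.

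**The case against.** The strongest reply is that the bias is conditional, and that its conditions may not be met.

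- **Completers must change on average.** This is correct: with no mean change there is no bias. However, the trial is planned around an improvement. Participants are also selected for an abnormal Step Quick Turn result, which is a primary outcome, so some regression to the mean is plausible even if the programme does nothing.
- **Dropouts must enter the contrast and lean toward the low half.** The text does not fully settle this. A dropout who returns no diary has missing rather than low adherence and may not be classifiable. Inclusion is still the plain reading of the intention-to-treat and missing-data statements. The 7 / 0 division is an upper bound; at 5 / 2 the test is close to its nominal level, although the estimate is still shifted by 0.9 deg/s.
- **The contrast is prespecified and asks only about a difference.** This stands, and it limits the harm.

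Three stronger readings are tempting and unsupported. A reader might infer that the plan is bound to produce a benefit of adherence; even in the worst division at planning values with ρ = 0.5–0.7, about 87–90% of trials with no adherence effect would show no significant difference. A reader might blame the median split, but continuous adherence analysed with the same imputed values would be biased in the same direction. A reader might also infer that the contrast will set exercise dose, but nothing in the protocol says so: the Intervention group activity section rests its dosage on a cited meta-analysis.

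**Conclusion.** The point holds as a conditional bias. Under the stated rules, dropouts contribute zero change to the adherence contrast. If they fall mainly in the low half and completers improve, the contrast leans toward a benefit of adherence. At planning values the spurious gap ranges from zero to about 2.1 deg/s, and the false-positive rate from about nominal to 10–13% (17% at ρ = 0.8). The size depends on three things that the documents do not give: the baseline correlation, where the dropouts fall, and the mean change in completers.

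The median split has separate, lesser weaknesses. It discards information about the degree of adherence, and it compares self-selected halves of about 17 each, with nothing in the section marking the result as exploratory. The randomised comparison is unaffected by this analysis, so the change is worth making but is not critical to the trial's main conclusion.

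**What to change.** Replace the adherence sentences in the Statistical analysis section with wording to this effect:

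> Among exercise participants with an observed 16-week assessment, the 16-week outcome will be regressed on adherence as a continuous measure (percentage of prescribed sessions logged), adjusted for the baseline value. Carried-forward values will not be used in this analysis. The result is exploratory and describes a non-randomised association.

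Dropping the carried-forward values removes the artefact. Continuous adherence answers the separate complaint about lost information, and the label answers the one about self-selection.

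The cost is small, since it changes wording and needs no new data. The simple two-group table is lost. The analysis is restricted to completers, and people who adhere well may still differ from those who do not in ways that affect balance, so self-selection remains and the exploratory label is needed.
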